### Assignment of interventions: allocation

#### Sequence generation {16a}

Participating municipalities were randomized on a site level to take part in either the first wave (2018) or the second wave (2019) of training and implementation of the intervention. Seven municipalities that constitute the original sample were randomized in 2018 to receive MTB training in either 2018 or 2019. Six municipalities constituted a site each, while the seventh, a larger municipality supplied four teams that were randomized as four additional sites. We, therefore, randomized 10 units. The municipalities were informed about allocation immediately after the randomization was conducted.

#### Concealment mechanism {16b}

Each municipality was given a letter (A, B, C, D, E, and F), and the four teams in the larger municipality (G) were numbered from 1 to 4. We applied block randomization with fixed block sizes: the first six municipalities were allocated in a 2:1 ratio so that two municipalities were assigned in the first wave, and four were assigned to the second wave. The uneven allocation ratio was the result of restrictions in training capacity in the initial study phase. For site G with four teams, we received the names of the clinicians in each of the four teams before randomizing the teams 1:1 to either the first or the second wave of training.

#### Implementation {16c}

Randomization was conducted by the trial statistician. Allocations of individual mothers are contingent on the wave a given site is allocated to. All seven original municipalities recruited CAU families before they received training. To secure enough CAU families, most municipalities continued to recruit CAU participants after receiving MTB training. This is the case if the MTB team is full or if the family is recruited very close to term.

Because recruitment was slower than expected and one of the seven original municipalities dropped out before training in 2019, we had to add four municipalities to the study in 2019 and 2020. These four municipalities could not be randomized because there was only one training session available when they joined the study. One municipality that had been trained in MTB before the trial started was added in 2019. This municipality did not have a CAU treatment and therefore only supplied MTB families to the study. One municipality was recruited before training in 2019 (wave 2) and two municipalities were recruited in 2020 where an extra training session was offered due to external funding (wave 3). The three municipalities recruited control families before training, and recruited intervention and control families after receiving training following the same guidelines as the original municipalities.

The municipality that joined before the 2019 training decided to discontinue the MTB intervention. They will continue the MTB intervention until the recruited intervention families graduate and will continue recruiting CAU families for the study.

### Assignment of interventions: blinding

#### Who will be blinded {17a}

As the intervention is a home visiting intervention, participants and care providers cannot be blinded. Outcome assessors, coders, and data analysts will be blinded.

#### Procedure for unblinding if needed {17b}

N/A as participants and clinicians cannot be blinded to treatment allocation.

### Data collection and management

#### Plans for assessment and collection of outcomes {18a}

Data are collected at five time points: T0: baseline immediately after recruitment, T1: baseline part two before the child is born, T2: when the infant is 3 months old, T3: when the infant is 12 months old, and T4: when the infant is 24 months old.

Data are collected through a secured online survey database (SurveyXact). Participants receive a text message or an email with a direct link to the questionnaire. They receive two automatic reminders and additional reminders if needed. The second part of the baseline questionnaire at T1 is collected at a home visit and includes questions about adverse childhood experiences and PTSD symptoms. At T3 and T4, when the child is 12 and 24 months old, mothers are also asked to record and upload a 6-min video of mother and child playing together. The video can be recorded by the family, at a home visit by clinicians from the municipality or trial staff, or through a Zoom-meeting with trial staff.

#### Plans to promote participant retention and complete follow-up {18b}

If the mothers need help to fill out the questionnaire, they can get support from a member of the trial staff or help from a clinician. Mothers receive a DKK 150 (~EUR 20) electronic gift card at each of the four data collections (baseline T0+T1, T2, T3, and T4). They will receive an additional DKK 300 (~EUR 40) for providing a video at T3 and T4. The research team will closely monitor the data collection process and send a monthly status report on data collection to all municipalities. As part of their monitoring of the data collection, the research team contacts participants by text message and phone calls.

The research team works closely with the clinicians in the municipalities to keep participants in the study and to collect data. Families who discontinue the intervention will still be kept in the study unless they specifically express that they wish to withdraw from the study.

#### Data management {19}

Municipal frontline workers enter the participants into a secured online survey database where after research staff enters the participant information into a database kept at a server at the Danish Agency for Governmental IT Services. The data platform conforms to the international ISO27001 standard on how to manage information security. Questionnaire data will be collected directly from the participants through a secured online survey database and will afterwards be transferred to the secure server.

#### Confidentiality {27}

All data are subject to confidentiality and will be handled in accordance with the General Data Protection Regulation (GDPR) and with the Danish legal regulations regarding data protection and security. Access to the data will be strictly limited to members of the research team.

#### Plans for collection, laboratory evaluation, and storage of biological specimens for genetic or molecular analysis in this trial/future use {33}

N/A as we do not collect any biological data.

### Statistical methods

#### Statistical methods for primary and secondary outcomes {20a}

The treatment effect of MTB relative to CAU on the primary outcome (parental sensitivity at child age 12 and 24 months) is analyzed as the mean change from baseline to post-intervention using ordinary least squares regressions separately. The analysis will be adjusted for stratification variables (municipality) and the baseline value of the outcome variable. Variables with indications (*p* < 0.1) of differences between intervention and CAU groups at baseline are also used as control variables. The treatment effect is estimated as a fixed effect using a binary indicator of MTB treatment, and cluster-robust standard errors based on wild bootstrap are used for inference. We evaluate the longitudinal effects separately for the 12-month and 24-month measurements. Two-sided tests with 0.05 significance levels are applied throughout. Analyses of secondary outcomes will be conducted analogously with follow-up analysis at child age 3 months in addition.

Additional exploratory analyses will be carried out in a generalized linear mixed models framework permitting the estimation of flexible nonlinear time patterns to examine the potential heterogeneity of treatment effect sizes across follow-up points.

To avoid the inflation of type 1 error due to multiple outcomes being tested simultaneously, we calculate the false discovery rate (FDR) on the secondary outcomes. In addition, we perform a sensitivity analysis using a Seeming Unrelated Regression framework to collectively examine treatment across all primary and secondary outcomes at age 12-month and 24-month follow-up, hence accounting for the covariance of outcomes.

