## Methods: participants, interventions, and outcomes

### Study setting {9}

The study is conducted in 11 Danish municipalities. Most of the municipalities are medium-sized with populations ranging from 45,600 to 89,800, but the trial also includes three small municipalities with populations ranging from 26,000 to 38,000, and one larger municipality with a population of 350,000. Seven municipalities were randomized in 2018 on a site level to either the first wave (2018) or the second wave (2019) of clinical training and implementation of the intervention. Because recruitment was slower than expected, we added four municipalities to the study in 2019 and 2020. These four municipalities could not be randomized because there was only one clinical training session available when they joined the study. All municipalities recruit CAU participants from the beginning of the recruitment period and until they receive training. Once the clinicians have received training in MTB, they start recruiting intervention families. To secure enough CAU families, most municipalities continue to recruit CAU participants after receiving MTB training. To avoid contamination, municipalities have been asked to not let MTB clinicians handle control families.

Table 1 shows which year the 11 municipalities received clinical training and whether they were randomized or not.

**Table 1 Tab1:** When the participating municipalities received training and whether they were randomized or not

Municipality	Randomized	MTB Teams	Training in 2018	Training in 2019	Training in 2020	Population
A	Yes	1	x			Small
B	Yes	2		x		Medium
C	Yes	2		x		Medium
D	Yes	2	x			Medium
E	Yes	2		x		Medium
F	Yes	0		(x)		Small
G	Yes	4	x	x		Big
H	No	1				Medium
I	No	2		x		Medium
J	No	2			x	Medium
K	No	2			x	Small

(x) the municipality withdrew from the study before training in 2019. Small: population <40,000; medium: population ≥40,000 and <100,000; big: >250.000

The flow chart is presented in Fig. 1.

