### Sample size {14}

Power analysis was carried out in the design phase to assess the statistical power for testing the main hypothesis. The power calculation is based on a meta-analysis of interventions aimed at improving parenting sensitivity [57]. The overall average effect size was 0.44 (standardized mean difference, SMD). We expect controls to constitute about one-third of the sample. For normally distributed outcomes and using a two-sided alpha of 0.05, and a beta of 80%, we would need a total of 183 participants (61 control and 122 intervention) for an effect size of 0.44 SMD. To leave room for dropout, we plan to recruit 250 participants (75 control and 175 intervention).

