In this study, the process for recruitment and data collection has been tailored to this exact group of pregnant women to increase the chance of recruiting the planned number of participants and retaining them in the study. Currently, we have collected baseline measures for 254 participants making this study the largest study of MTB. Maternal sensitivity is the primary outcome of the study and collecting video recordings from the participants is therefore pivotal. Some women refuse to submit a video recording at child age 12 and 24 months, perhaps because they fear being judged as a parent. To collect as many videos as possible, we have developed different possible procedures for video recordings (including home visits by either a known person or by independent trial staff), recording the video by the participant without any help or recording it by zoom with trial staff) and have produced a short informational video about the video recording. We will closely monitor referral, recruitment, and retention rates through the study and accommodate procedures if needed.

The study has recruited participants from June 2018 and will continue to recruit until the end of May 2022. This is a period where several historical events have taken place and impacted the study. GDPR was introduced in Europe in May 2018 right before recruitment started with many new laws concerning processing personal data for research purposes making it difficult to produce recruitment materials. Consequently, it took longer time to finalize data agreements with several municipalities. The focus on data leaks and the importance of the GDPR also made some participants wary of handing over sensitive and personal information. The Covid-19 pandemic also has affected the trial. Since March 2019, Denmark has experienced different levels of lockdown and restrictions challenging recruitment, intervention, and outcome assessment. Furthermore, Denmark experienced a strike among nurses from June 19 to August 28, 2021, where some of the health nurses were affected.

In sum, there is a need for early interdisciplinary interventions for parents and infants at increased risk for adversity. The present study of MTB in a Scandinavian context has the potential to improve the well-being of parents and infants at increased risk for adversity and to prevent health inequalities in the long run.

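### The primary model names neither calendar time nor gestational age at recruitment, although the recruitment scheme ties both to the arm a woman enters

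*Protocol article*

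**What the plan says.** **Allocation.** Under Study setting {9}: "All municipalities recruit CAU participants from the beginning of the recruitment period and until they receive training". MTB enrolment starts only once the clinicians are trained. Most municipalities keep enrolling CAU women after that, and Implementation {16c} gives the reason: "This is the case if the MTB team is full or if the family is recruited very close to term". No figure is given for how many CAU women come before or after training.

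**What was randomised.** Sequence generation {16a} and Concealment mechanism {16b} describe ten units randomised to a 2018 or 2019 training wave: six municipalities, and four teams inside municipality G split 1:1. Four further municipalities were added without randomisation. One of these supplies MTB families only. Another gives up MTB but goes on recruiting CAU.

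**Model.** Section {20a}: "The analysis will be adjusted for stratification variables (municipality) and the baseline value of the outcome variable". The next sentence adds any variable that differs between arms at baseline with p < 0.1. The estimate is the coefficient of a binary MTB indicator in ordinary least squares, fitted separately at 12 and 24 months.

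**Period.** Of the roughly four years of recruitment the Discussion says: "This is a period where several historical events have taken place and impacted the study". It names data-protection law, Covid-19 restrictions and a nurses' strike.

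**The concern.** In a staggered roll-out, arm and calendar time are linked by construction. The staggered start dates can separate the two, but only if time is in the model. Here it is not. Anything that changed between 2018 and 2022 (case mix, usual care, the way videos were obtained, family life under restrictions) can pass into the MTB coefficient.

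The CAU women enrolled after training were enrolled alongside MTB women, so they would help with the time problem. They were diverted by capacity or by late recruitment, however, so they may differ in other ways. Gestational age at recruitment, which marks one of these two routes, is also not in the model.

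At stake is whether a positive or a null result can be attributed to MTB at all.

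**Working it through.** **1. What the stated covariates can absorb**

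| Term in {20a} | Does it deal with enrolment date or late recruitment? |
|---|---|
| Municipality | No. It removes stable differences between municipalities. The early/late contrast among the teams in G survives it. |
| Baseline value of the outcome | Not for the primary outcome. Table 2 schedules the CIB video at T3 and T4 only. |
| Variables with p < 0.1 at baseline | Only by chance. Neither enrolment date nor gestational age is among the listed baseline measures, and a significance trigger is no commitment. |
| Time patterns in the exploratory mixed models | No. These run across follow-up points, not calendar dates. |

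**2. The protocol's own sample size**

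Inputs from Sample size {14}: "using a two-sided alpha of 0.05, and a beta of 80"% (read as 80% power); "The overall average effect size was 0.44 (standardized mean difference, SMD"); "We expect controls to constitute about one-third of the sample".

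- Controls = (1.960 + 0.842)² × (1 + 1/2) / 0.44² = 60.8, rounded up to 61.
- Total = 3 × 61 = 183. This agrees with the stated "total of 183 participants (61 control and 122 intervention").
- SE = √(1/61 + 1/122) = 0.157 SD, and power = Φ(0.44/0.157 − 1.96) = 80.1%.

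**3. Gap in enrolment date within a site**

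Assume even accrual over 4 years in a site trained τ years after the start.

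- Mean enrolment time before training: τ/2.
- Mean enrolment time after training: (τ + 4)/2.
- Difference: 2 years, whatever τ is.
- If a share p of CAU women is enrolled after training, the MTB-minus-CAU gap is 2(1 − p) years.

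A site that joins s years late has a maximum gap of (4 − s)/2 years, for example 1 year at s = 2. The added municipalities would therefore pull the average gap down.

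**4. Bias without a time term**

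Bias = trend × gap. The trend is assumed; the protocol gives none. At 0.1 SD per year:

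| CAU enrolled after training (p) | Gap, years | Bias, SD | Share of 0.44 |
|---|---|---|---|
| 0% | 2.0 | 0.20 | 45% |
| 25% | 1.5 | 0.15 | 34% |
| 50% | 1.0 | 0.10 | 23% |
| 75% | 0.5 | 0.05 | 11% |
| 100% | 0 | 0 | 0% |

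A simulation confirmed these values to within 0.003 SD. It used 61 CAU and 122 MTB women, 12 sites (with the teams in G as separate sites) trained about 0.5, 1.3 or 2.3 years in, site effects in the model, no clustering and 1,500 replicates. Adding linear calendar time brought the bias to about 0 in every row.

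Type I error = 1 − Φ(1.96 − bias/0.157) + Φ(−1.96 − bias/0.157). With a 1-year gap, trends of 0.05, 0.10 and 0.20 SD per year turn the nominal 5% into about 6%, 10% and 25%.

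**5. Price of the time term**

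Variance ratio (site effects plus linear time, against site effects alone) from the same simulation. Power at 183 = Φ(0.44/(0.157 × √ratio) − 1.96).

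| p | Variance ratio | SE increase (√ratio − 1) | Power at 183 | N for 80% |
|---|---|---|---|---|
| 0% | 2.79 | 67% | 39% | about 510 |
| 25% | 1.65 | 28% | 59% | about 302 |
| 50% | 1.26 | 12% | 71% | about 230 |
| 75% | 1.07 | 3% | 77% | about 196 |

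These power figures ignore clustering and the cost of the site effects themselves.

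**The case against.** **The protocol is partly open about this.** It calls the design quasi-cluster, says an individual's arm depends on the wave of her site, and lists the sites that were not randomised. This stands as disclosure, but disclosure does not change the estimate. Nor is the matter simply left to an analysis plan, because {20a} fixes the primary model and its covariates.

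**The p < 0.1 rule might bring time in.** If enrolment date counted as a baseline variable, a large imbalance would probably trigger the rule. This is a real but weak safeguard, for the reasons in the first table.

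**A reader might infer that CAU is recruited mainly before training.** The documents do not say so. The wish to secure enough CAU families suggests that the later share may be substantial. A larger later share reduces confounding with time but gives more weight to overflow selection.

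**A reader might infer that municipality adjustment removes the randomised contrast altogether.** It does not, because two early and two late teams were randomised inside G, the largest municipality.

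**A reader might infer that all CAU women enrolled after training were recruited late.** The full-team route is a capacity rule with no stated link to gestational age, and the share using each route is unknown.

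**The drift is hypothetical.** The Discussion describes events, not a steady trend. With outcomes at 12 and 24 months, some early CAU women were also assessed during the restrictions. The site that drops MTB but keeps recruiting CAU lowers the imbalance further. All of this stands against any claim of a known size or direction.

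**Conclusion.** The concern holds as a fault in the stated primary model. Arm is tied to enrolment date within sites, and partly to closeness to term, and no fixed covariate addresses either. Outside G, the estimate is largely a before/after plus overflow comparison.

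The size of the bias cannot be derived from the protocol, and its sign is unknown. The range of about 0 to 0.20 SD rests on an assumed trend of 0.1 SD per year, even accrual, and every site recruiting from the start; late-joining sites would reduce it. Selection through the full-team and near-term routes is not quantified here and would come on top. The documents do not support saying that MTB will look better than it is, only that a trend and a treatment effect cannot be told apart as planned.

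**What to change.** In {20a}, make these changes before the outcome data are analysed:

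1. Prespecify two fixed covariates in the primary model beside municipality (team within G): calendar period of enrolment, as period indicators or a smooth term, and gestational age at recruitment. Neither should depend on the p < 0.1 rule.
2. Add two sensitivity analyses: one restricted to the randomised sites with period effects, and one separating CAU women enrolled before training from those enrolled after it.
3. State that individual-level allocation is non-randomised and interpret the effect accordingly. Gestational age cannot remove selection through the full-team route.
4. Restate the achievable precision once the split of CAU before and after training is known.

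**Cost.** The change is one of wording. Enrolment timing and the interval to birth should be obtainable, since women are registered after consent and births are reported to the research team. The real price is precision: the standard error rises by roughly 3% if 75% of CAU women come after training, and by 67% if none do, with a linear time term. In a second assumed layout (training at months 3, 15 and 27; 10–30% of post-training recruits in CAU), half-year indicators cost 10–22%, but that should not be taken as an upper limit. Splitting the planned 75 CAU women will also leave small groups, so the second sensitivity analysis can be supportive only.

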#### Baseline measures

In addition to the socio-demographic measures, we include the following measures at baseline to assess the initial level and to account for them as possible moderators or confounders in the effect analyses.

The Prenatal Parental Reflective Functioning Questionnaire (P-PRFQ) [76] is a 14-item measure of *parental reflective functioning* or the pregnant woman’s ability to mentalize. The P-PRFQ is an adaptation of the PRFQ [77] and consists of three subscales: opacity of mental states (4 items), reflecting on the fetus-baby (5 items), and the dynamic nature of mental states (5 items). Cronbach’s alpha is 0.77 for the total score and 0.69–0.77 for the three subscales. Responses are on a Likert scale ranging from 1 to 7 with three different scales: (1) High-Low where 7 = optimal PRF, 1 = low PRF; (2) Low-High where 1 = optimal PRF, 7 = low PRF, and (3) Middle where 4 = optimal PRF, 1 and 7 = low PRF. The total score range is 7–98.

The Hospital Anxiety and Depression Scale (HADS) [78, 79] is a 14-item measure of *anxiety and depression*. HADS consists of the two subscales “anxiety” and “depression,” both ranging from 0 to 21, where low scores indicate less anxiety and depression.

The Experiences in Close Relationship Scale-Short Form (ECR-S) [80] is a 12-item measure of *adult attachment* consisting of the two subscales: “Anxiety” (fear of abandonment and a craving for interpersonal closeness) and “avoidance” (fear of intimacy and interpersonal dependency). Each subscale ranges from 1 to 42, where low scores indicate better attachment.

The Childhood Trauma Questionnaire (CTQ) [81] is a 28-item measure of adverse childhood experiences (ACE). Items are rated on a 5-point Likert scale (Never true, Rarely true, Sometimes true, Often true, Very often true). The CTQ consists of five subscales: emotional abuse, physical abuse, sexual abuse, emotional neglect, physical neglect, and a minimization/denial subscale. Each subscale ranges from 5 to 25, where low scores indicate less trauma experience.

The PTSD-8 inventory [82] is an 8-item measure of *posttraumatic stress disorder (PTSD) symptoms*, including intrusion, avoidance, and hypervigilance. The total score range is 8–32, where a low score indicates a lower level of PTSD.

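### Choosing control variables by a p<0.1 test of baseline difference can leave prognostic confounders out of the primary model, in a comparison that depends on covariate adjustment

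*Protocol article*

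**What the plan says.** In the section on statistical methods for primary and secondary outcomes ({20a}), maternal sensitivity at 12 and 24 months is analysed by ordinary least squares with a binary treatment indicator. The fixed part of the adjustment is: "The analysis will be adjusted for stratification variables (municipality) and the baseline value of the outcome variable". The rest is selected from the data: variables with p<0.1 indications "of differences between intervention and CAU groups at baseline are also used as control variables". No other covariate is named for this model.

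Under Baseline measures, the questionnaires are collected to assess the initial level and "to account for them as possible moderators or confounders in the effect analyses". The only rule for using them as confounders in the primary analysis is the screen above.

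Three other places bear on the point:

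- **Allocation ({16a}–{16c}).** Ten units in seven municipalities were randomised to a training wave. A mother's arm then follows from when she is recruited. After training, it also depends on whether the team has room and how near she is to term. Four of the 11 municipalities were not randomised, and one supplied intervention families only.
- **Timing (Table 2 and {18a}).** The interaction video that yields the primary outcome is recorded only at 12 and 24 months.
- **Second baseline part ({18a}).** For CTQ and PTSD-8: "The second part of the baseline questionnaire at T1 is collected at a home visit".

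**The concern.** A test of baseline difference asks whether the arms differ by more than chance would produce. Confounder control asks something else: whether a variable predicts the outcome and differs between the arms, by whatever amount. The screen ignores the first part and makes the second depend on sample size. A strong predictor of sensitivity with a moderate imbalance can stay out, while an irrelevant variable with a chance imbalance goes in.

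In an individually randomised trial with a baseline measure of the outcome, this would matter little. Here the arms may differ systematically through calendar time, team capacity and closeness to term, and municipality adjustment does not remove differences between women within a municipality. The planned adjustment for the baseline outcome value cannot be made for maternal sensitivity, because no such value exists. Residual confounding in the primary estimate is at stake, along with the precision that prognostic covariates would bring.

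**Working it through.** **Inputs.** From Sample size {14}: SMD 0.44, two-sided alpha 0.05, 80% power, one control to two intervention, 183 analysed (61 + 122), 250 recruited (75 + 175). From {20a}: selection at p<0.1. The documents give no imbalances, covariate–outcome slopes or correlations between covariates, so those below are assumptions.

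**The plan's own figure.** Controls needed = (1.960 + 0.842)² × (1 + 1/2) / 0.44² = 7.85 × 1.5 / 0.1936 = 60.8, so 61 controls and 183 in total. This matches the plan.

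**Imbalance needed to enter.** Threshold = 1.645 × sqrt(1/75 + 1/175) = 1.645 × 0.138 = 0.227 SD (0.228 with the t quantile). At 61 v 122 it is 0.258 SD.

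**Probability that a true imbalance d is missed.** This is 1 − [Φ(d/se − 1.645) + Φ(−d/se − 1.645)], with se = 0.138 at 75 v 175.

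| True imbalance (SD) | Missed, 75 v 175 | Missed, 61 v 122 |
|---|---|---|
| 0.10 | 81% | 83% |
| 0.15 | 71% | 75% |
| 0.20 | 58% | 64% |
| 0.25 | 43% | 52% |
| 0.30 | 30% | 39% |

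**Chance entry.** With k independent covariates that are truly balanced, at least one enters with probability 1 − 0.9^k: 41% for k = 5, 65% for k = 10, 88% for k = 20.

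**Effect on the estimate.** Simulation with no treatment effect, 75 v 175, OLS, 4,000 runs per row, and four independent confounders imbalanced in the same direction. Municipality effects, clustering and the wild bootstrap are left out. Each cell gives absolute bias in SD and type I error.

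| Slope per SD | Imbalance each | No adjustment | p<0.1 screen | All four fixed |
|---|---|---|---|---|
| 0.3 | 0.15 | 0.178, 25% | 0.072, 7.2% | 0.000, 4.5% |
| 0.3 | 0.20 | 0.242, 41% | 0.078, 7.9% | 0.002, 4.8% |
| 0.3 | 0.30 | 0.359, 73% | 0.051, 7.1% | 0.000, 5.2% |
| 0.4 | 0.15 | 0.238, 40% | 0.095, 8.5% | 0.000, 5.4% |
| 0.4 | 0.20 | 0.320, 64% | 0.100, 9.8% | 0.001, 5.2% |
| 0.4 | 0.30 | 0.477, 93% | 0.069, 8.2% | 0.001, 4.6% |

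With a single confounder at the same imbalances and slopes, screening leaves 0.011–0.025 SD and type I error stays at about 5%.

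**A longer list.** Take 12 covariates, six of them confounders with 0.2 SD imbalance each. Unadjusted bias is 6 × 0.2 × slope, that is 0.18 SD at slope 0.15 and 0.24 SD at slope 0.20.

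- Independent covariates: the screen leaves 0.058 SD with type I error 6.9% (slope 0.15) and 0.074 SD with 8.2% (slope 0.20). The full set gives 0.001 SD with 5.4% and −0.001 SD with 5.0%. At slope 0.20 the standard error is 0.127 with the full set and 0.136 with the screen.
- Slope 0.175, varying the pairwise correlation: screened bias and type I error are 0.069 SD and 7.6% at correlation 0, 0.016 SD and 5.9% at 0.3, and 0.015 SD and 9.8% at 0.5.

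**The case against.** The strongest reply has four parts.

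- **The rule is stated in advance and looks only at baseline data.** It gives no room to pick covariates for a favourable result. That stands. A reader might infer outcome-driven model selection, and the text does not support it. What remains is that the covariate list is unknown until the baseline data are in and is chosen on the wrong criterion.
- **No confounding has been shown.** A reader might infer that real confounders are left out, or that the trial is simply non-randomised. The article reports no baseline imbalance and no covariate–outcome association, so the documents support only that the rule can leave confounders out. The training wave was randomised for the original seven municipalities. It is individual mothers, and the four added municipalities, that were not randomised.
- **The screen does useful work and the size depends on assumptions.** In the four-confounder table it removes between 60% (0.178 to 0.072) and 86% (0.359 to 0.051) of the unadjusted bias. With correlated covariates, which is plausible for age, education, cohabitation and financial strain, the remaining bias is small. The fixed set does well partly by construction, because it contains every simulated confounder. All of this stands and limits the size, but it does not make the screen the better choice.
- **Standard errors.** A reader might infer that ignoring the selection step makes the standard errors too small in general. With independent covariates, model and empirical values agree (0.137 and 0.137 at slope 0.175), and the excess type I error comes from residual bias. With four balanced covariates the screened test is conservative (2.2–3.6%). Only at correlation 0.5, where bias is small but type I error is 9.8%, must something other than bias be at work. The claim is not made in general here.

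It might also be thought that the first baseline questionnaire (T0) is safe because it precedes knowledge of the arm. It follows recruitment, and families are offered one condition or the other at invitation, so the arm is probably known at T0 as well. What is specific to T1 is the home-visit collection and the possibility of early contact with the intervention.

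**Conclusion.** The concern holds as a weakness in a rule that the protocol itself fixes; it is not a detail left to an analysis plan. The screen is the only individual-level confounder control stated for the primary outcome beyond municipality, and at the planned size it misses a 0.20 SD imbalance more often than it finds it.

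The likely damage ranges from slight to moderate: about 0.01–0.02 SD with one confounder or correlated covariates, up to 0.10 SD with four strong independent confounders in the same direction. Against the design effect of 0.44, that is 0.01/0.44 = 2% to 0.10/0.44 = 23%. Type I error lies at about 5–10% in the confounded scenarios examined. The direction of any bias in this trial is unknown.

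That the rule exists and is poorly suited to this design is certain. The size rests on assumed imbalances, slopes and correlations, with clustering ignored, and should be read as a range. The change should be made, but the screen is inferior to a fixed set, not worthless.

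**What to change.** Delete the p<0.1 rule. Before any outcome analysis, name the covariates for the primary model from T0 measures that the article already collects and lists under Baseline measures or as subgroup variables ({20b}): maternal age, parity, education, single or cohabiting, financial strain, HADS, ECR-S and P-PRFQ. Keep municipality. Use the same list for every outcome, whatever the baseline p-values.

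Handle three further variables separately:

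- **CTQ and PTSD-8:** add them in a sensitivity analysis. Childhood trauma is a plausible confounder, but these T1 measures are taken at a home visit, where collection or early contact may differ by arm.
- **Calendar period:** also a sensitivity analysis. It is strongly tied to arm, since only control families are recruited before training, and including it may widen the standard error materially.
- **Gestational age at recruitment:** use it only if it is recorded; Table 2 does not list it.

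The cost is a wording change and a few degrees of freedom. Entering two HADS subscales, two ECR-S subscales, a P-PRFQ total and five single terms uses 2 + 2 + 1 + 5 = 10, against 183 analysed participants. No new data are needed.
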